#### Participant feedback

At the end of the intervention, participants will complete an in person 60 min semistructured qualitative interview with a member of the research team with guiding questions centred around two key themes: (1) feasibility of the programme and (2) running-related beliefs.

#### Physical assessments

Both anthropometry and physical capacity (muscle flexibility, strength and power) will be quantified at baseline only. Outcomes will facilitate safety regarding exercise prescription and serve as potential confounding factors in statistical analyses. The following measures will be obtained using standard techniques: body mass, height, blood pressure, sit and reach,^65^ max single-leg calf raise,^66^ 30-second single-leg sit to stand,^67^ triple hop for distance^68^ (online supplemental appendix C).

### Participant timeline

Recruitment commenced on 3 October 2022 and will continue until 40 participants are enrolled. All participants will attend face-to-face data collection at baseline, 6 and 12 weeks post baseline (figure 1). Participants allocated to exercise training will commence the week of baseline data collection and continue until 12-week postbaseline data collection.

**Figure 1 F1:**
[figure not shown]
Study flow diagram.

### Sample size

In line with recommendations,^69^ the current study was designed to detect the smallest effect size of interest between the intervention and control for each primary outcome (IVD T2, pain intensity and disability) at 12 week follow-up assuming an α of 0.05, β of 0.8 and adjustment for test–retest reliability.^70^ To detect a between-group net difference in IVD T2 of d=0.183 based on a minimum detectable change of 5.1 ms,^30^ SD of 27.9 ms^30^ and test–retest reliability of r=0.97,^30^ 28 total participants are required (n=14 per group). To detect a between-group net difference in pain intensity of d=1.00 based on a clinically meaningful change of 20 mm,^34^ SD of 20 mm^71^ and the most conservative test–retest reliability of r=0.57,^35^ 16 total participants are required (n=8 per group). To detect a between-group net difference in disability of d=0.52 based on a clinically meaningful change of 10 points,^72^ SD of 19.2 points^73^ and test–retest reliability of r=0.83,^72^ 20 total participants are required (n=10 per group). To account for a conservative attrition rate of 30%, despite retaining 80% of CLBP participants throughout our previous 6 month randomised controlled trial,^10^ 40 total participants (n=20 per group) will be recruited to detect the three primary outcomes smallest effect estimates of interest. All power calculations were conducted using G*Power (V.3.1.9.7).^74^

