IVD T2 (primary outcome)^12^: Individual lumbar IVD T2 (in ms) will be calculated by a linear fit of the natural logarithm of the image intensity across the eight echo times of the T2 Sag spin-echo multiecho sequence. IVD T2 will be calculated for the entire IVD and five equidistant subregions (anterior annulus, anterior nucleus, centre nucleus, posterior nucleus, posterior annulus).^14^ Lumbar IVD T2 has excellent test–retest reliability (ICC=0.98).^30^IVD height and volume^12^: Individual lumbar IVD height will be calculated from the T2 Sag spin-echo multiecho sequence. IVD volume will then be calculated by multiplying the area of each slice by the slice thickness and gap between slices.Nucleus–annulus signal intensity ratio^14^: T2-weighted Sag sequences will be used to determine the signal intensity of five equidistant subregions (anterior annulus, anterior nucleus, centre nucleus, posterior nucleus, posterior annulus) to calculate the nucleus–annulus signal intensity ratio.Paraspinal muscle volume and size^31^: Axial mDIXON sequences will be used to calculate muscle size and volume of the paraspinal muscles of multifidus, erector spinae, psoas major and quadratus lumborum. For these, we will primarily report on paraspinal cross-sectional muscle volume (cm^3^). Lumbar paraspinal muscle volume will be calculated by multiplying the area of each lumbar slice by the slice thickness plus the gap between slices. Lumbar level-specific average area (mm^2^) will also be calculated.Paraspinal muscle fat fraction^31^: Axial mDIXON sequences will be used to calculate the paraspinal fat fraction. The fat fraction will be calculated as 100%×signal intensity fat/(signal intensity fat+signal intensity water).Vertebral body fat fraction^28^: Sag mDIXON sequences will be used to calculate the vertebral body fat fraction. The fat fraction will be calculated as 100%×signal intensity fat/(signal intensity fat+signal intensity water).IVD to vertebral body height ratio^14^: Sag mDIXON sequences will be used to calculate the vertebral body height. This will then allow for calculating IVD height to vertebral body height ratio.Pfirrmann grading^32^: T2-weighted Sag sequences will be used to complete the radiographic grading of the IVDs using the Pfirrmann criteria.

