### Statistical methods

Linear mixed models with random effects (participants) and an intention-to-treat approach will be used to evaluate within-group and between-group changes by time. All linear mixed models will allow for heterogeneity of variance according to study date and employ restricted maximum likelihood estimations. An α of 0.05 will be adopted for all analyses.

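### The stated sample sizes do not give 80% power on the protocol's own inputs: for IVD T2, 14 per group gives 48%, and 29–30 per group would be needed

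*Protocol article*

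**What the plan says.** The Sample size section aims to detect the smallest effect of interest on each of the three primary outcomes at 12 weeks, "assuming an α of 0.05, β of 0.8" and "adjustment for test–retest reliability". Its inputs and results are:

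- **IVD T2:** a "between-group net difference in IVD T2 of d=0.183 based on a minimum detectable change of 5.1 ms", SD 27.9 ms, "test–retest reliability of r=0.97"; 28 in total (14 per group).
- **Pain:** d=1.00 (20 on an SD of 20), r=0.57, described as the most conservative reliability; 16 in total (8 per group).
- **Disability:** d=0.52 (10 on an SD of 19.2), r=0.83; 20 in total (10 per group).

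The largest total, 28, is inflated for 30% attrition to 40 (20 per group), and the section says this suffices for all three primary outcomes. G*Power is named, but not the test family, the effect-size conversion or the sidedness. The Statistical methods section adds only that "An α of 0.05 will be adopted for all analyses".

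The Lumbar spine MRI section gives a second T2 figure from the same citation: "Lumbar IVD T2 has excellent test–retest reliability (ICC=0.98".

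**The concern.** A d of 0.183 is very small. Without any use of baseline it would take about 470 per group, so 14 per group rests almost wholly on the factor (1−r) and on that factor being applied correctly. If it was not, the trial claims a power for its first-listed primary outcome that it does not have, and a null T2 result could be read as evidence against a 5.1 ms effect that the trial was about as likely to miss as to find. The same method was presumably used for pain and disability, so an error in it would carry over to all three.

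**Working it through.** **Assumptions.** Two-sided α of 0.05, target power 0.80, 1:1 allocation, noncentral t. The contrast is the 12-week between-group difference, using baseline in one of two standard ways:

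- change score: SD × √(2(1−r))
- ANCOVA: SD × √(1−r²)

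**T2, change score.** √(2 × 0.03) = 0.2449, so the SD of change is 27.9 × 0.2449 = 6.83 ms and the standardised effect is 5.1/6.83 = 0.746. The normal approximation gives n = 2 × (1.960 + 0.842)²/0.746² = 28.2 per group; the exact t calculation gives 30.

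**T2, ANCOVA.** √(1 − 0.97²) = 0.2431, so the SD is 6.78 ms, the effect is 0.752, and the t calculation gives 29 per group.

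The protocol's 28 is therefore close to the number needed *per group*, but it is stated as the total. A one-sided test does not rescue it (23 per group by change score).

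**All three outcomes, on the protocol's own d and r** (ranges cover change score and ANCOVA):

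| Outcome | Stated n per group | n per group for 80% | Power at stated n | Power at 14 | Power at 20 |
|---|---|---|---|---|---|
| IVD T2 | 14 | 29–30 | 48% | 48% | 63–64% |
| Pain | 8 | 12–15 | 52–62% | 78–87% | 91–96% |
| Disability | 10 | 20–21 | 47–51% | 62–66% | 79–82% |

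Fourteen per group is also what remains of 20 after the planned attrition (20 × 0.70 = 14). At r=0.97 the T2 difference detectable with 80% power is about 7.5 ms with 14 per group and 6.2 ms with 20.

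**Where the stated totals may come from.** For a repeated-measures within–between interaction with m measurements, the noncentrality is λ = f²·N·m/(1−r). With m=3 and f=d/3 this returns exactly 28, 16 and 20. That f is too large for this contrast:

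- If the group difference grows linearly (0, d/2, d), then f = d/√24 = d/4.90.
- If it appears at one step (0, 0, d or 0, d, d), then f = d/√18 = d/4.24.

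With those values the T2 total is 72 or 54, not 28. The match is not unique. A two-measurement interaction with f=d/2.65 gives the same three totals, against a correct d/4. Dropping the factor 2 from the change-score variance gives 14.09, 6.75 and 9.84 per group before rounding, which is also near the stated figures. All of these overstate the effect entered.

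**Attrition.** 28/0.70 = 40, so this step is right.

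**The correlation itself.** Test–retest reliability describes repeat measurement in people who have not changed. The analysis needs the baseline-to-12-week correlation, which also absorbs true individual change and differing response and so is likely to be lower. The documents give no such value. As assumptions only:

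| Assumed r (T2) | n per group for 80% | Power at 14 | Power at 20 |
|---|---|---|---|
| 0.95 | 47–48 | 31–32% | 43–44% |
| 0.90 | 91–95 | 18–19% | 24–25% |

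**Consistency of the T2 inputs.** SEM = 27.9 × √0.03 = 4.83 ms. A 95% minimum detectable change would be 1.96 × √2 × 4.83 = 13.4 ms (10.9 ms at 0.98), against the stated 5.1 ms. To obtain 5.1 ms would take r of about 0.996 with this SD, or an SD of about 10.6 ms with r=0.97.

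**The case against.** The best defence is that the section does not name the test, so a calculation that differs from a two-group change score or ANCOVA is not thereby wrong. That is fair as far as the cause goes: the f=d/3 explanation is an inference from matching totals. It does not rescue the result, because a three-measurement interaction with the proper f needs more participants than stated, not fewer.

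A second defence is that 20 per group are recruited, not 8, 10 or 14. This has force for pain, which exceeds 90% power with full retention and started from a deliberately low reliability. It has some force for disability, which is near 80% if nobody drops out. It does not help T2.

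A reader might infer that T2 is underpowered *because* reliability was used for the correlation, or because the T2 inputs conflict. The documents do not support either as the cause. The shortfall is already there with r=0.97 taken at face value, so changing r alone would leave the main error in place. The conflicts, if resolved, could raise power: r=0.98 gives 64–65% at 14 per group and 80–81% at 20, while r=0.996, an SD of 10.6 ms or a 13.4 ms target would each give over 99% at 14. The retest interval is not stated, so the reliability cannot be called short-interval. The 13.4 ms figure holds only if a 95% minimum detectable change is meant, and an ICC of 0.98 and an r of 0.97 may be different statistics. These are queries about consistency.

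Nor should "assuming an α of 0.05, β of 0.8" be taken as a design with 20% power. It is a slip for power of 0.80.

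**Conclusion.** The point stands. On the protocol's own d and r, none of the three stated sample sizes gives 80% power under a standard analysis of the 12-week difference; each is roughly half to two thirds of what is needed. The consequence is most serious for T2, where power is 48% with the planned number of completers and 63–64% at best. Disability is short at 14 per group and borderline at 20. Pain is near or above target at 14 and comfortable at 20.

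This rests on a two-sided test and on the stated SDs and correlations being right. The faulty conversion is the probable cause, not a demonstrated one. The use of reliability in place of a 12-week correlation is a valid secondary point that would lower T2 power further, by an amount the documents cannot fix. It would go too far to say that the trial has little chance of detecting a T2 effect, since that depends on assumed correlations.

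**What to change.** Rewrite the Sample size section, keeping the enrolment at 40:

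1. Name the G*Power test, the sidedness and the effect-size conversion, and recompute with the conversion that fits a 12-week between-group difference in change.
2. Take the T2 SD, reliability and minimum detectable change from one T2 variable, state how the minimum detectable change is defined, and give one reliability value or explain why two appear.
3. Replace reliability with a baseline-to-12-week correlation, for example informed by the team's earlier 6-month trial, and show a sensitivity range.
4. Restate power, or the detectable difference, for all three primary outcomes at 14 and 20 per group.
5. Correct the β wording to power 0.80 (β=0.20).

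The cost is one paragraph and a less favourable statement of power for T2 and disability.

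### The stated sample sizes (28, 16 and 20 in total) are about half of what their own inputs require, and the planned trial has about 48% power, not 80%, for disc T2

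*Protocol article*

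**What the plan says.** The Sample size section says the trial was "designed to detect the smallest effect size of interest between the intervention and control for each primary outcome" at 12 weeks, "assuming an α of 0.05, β of 0.8 and adjustment for test–retest reliability". Three requirements follow:

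- **Disc T2:** a "between-group net difference in IVD T2 of d=0.183 based on a minimum detectable change of 5.1 ms", SD 27.9 ms and r=0.97; "28 total participants are required (n=14 per group").
- **Pain:** 20 mm, SD 20 mm (d=1.00) and r=0.57; "16 total participants are required (n=8 per group").
- **Disability:** 10 points, SD 19.2 points (d=0.52) and r=0.83; "20 total participants are required (n=10 per group").

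The largest total, 28, is raised to 40 for 30% attrition, and the section concludes that 40 recruits are enough for all three primary outcomes. G*Power is named as the software; the test family and sidedness are not given. Statistical methods adds only "An α of 0.05 will be adopted for all analyses" and plans linear mixed models of change over time.

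**The concern.** The inputs and outputs are both printed, so they can be checked against each other. A standardised difference of 0.183 is very small. Even a reliability of 0.97 turns it into an effect of only about 0.75 SD of change, and 14 per group is too few to detect that with 80% power. The same pattern appears for pain and disability.

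What is at stake is the justification for the size of the trial. T2 fixed the target of 40 and is the novel question. If its power is near one half, a non-significant T2 result says little about whether running changes the disc, yet readers would take it as coming from an adequately powered trial.

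**Working it through.** **Inputs** (Sample size section): difference, SD and r as listed above; α 0.05; power 0.80. Two-sided testing is assumed because sidedness is not stated.

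**Figures that reproduce.** 5.1/27.9 = 0.183; 20/20 = 1.00; 10/19.2 = 0.52; 28/0.7 = 40.

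**Figures that do not.** A net difference adjusted for test–retest reliability is a between-group difference in change, with

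SD of change = SD × √(2(1 − r)).

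The more favourable alternative is a baseline-adjusted comparison, with

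residual SD = SD × √(1 − r²).

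| | T2 | Pain | Disability |
|---|---|---|---|
| SD of change | 27.9×√0.06 = 6.83 | 20×√0.86 = 18.5 | 19.2×√0.34 = 11.2 |
| Effect in those SDs | 0.746 | 1.078 | 0.893 |
| n per group, normal formula 2(1.96+0.842)²/effect² | 28.2, so 29 | 13.5, so 14 | 19.7, so 20 |
| n per group, noncentral t | 30 | 15 | 21 |
| Residual SD, baseline-adjusted | 6.78 | 16.4 | 10.7 |
| n per group, noncentral t | 29 | 12 | 20 |
| **Stated n per group** | **14** | **8** | **10** |

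On change scores the totals needed are 60, 30 and 42 against 28, 16 and 20 stated, that is 47%, 53% and 48% of the need. Inflating 60 for 30% attrition gives 60/0.7 = 86, against 40 planned.

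**Power** (noncentral t; change score, then baseline-adjusted):

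| Size | T2 | Pain | Disability |
|---|---|---|---|
| Stated n (14, 8, 10 per group) | 0.48, 0.48 | 0.52, 0.62 | 0.47, 0.50 |
| 28 completers | 0.48, 0.48 | 0.78, 0.87 | 0.62, 0.66 |
| 40 completers | 0.63, 0.64 | 0.91, 0.96 | 0.79, 0.82 |

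**Difference detectable with 80% power** (change score, then baseline-adjusted):

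| Size | T2 (ms) | Pain (points) | Disability (points) |
|---|---|---|---|
| 28 completers | 7.5, 7.5 | 20.4, 18.1 | 12.3, 11.8 |
| 40 completers | 6.2, 6.2 | 16.9, 15.0 | 10.2, 9.7 |

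**Other readings tried.**

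- One-sided testing needs 23, 12 and 17 per group on change scores and 23, 10 and 15 baseline-adjusted. Only pain comes near its stated n, and none reaches it.
- The Lumbar spine MRI section gives a different reliability: "Lumbar IVD T2 has excellent test–retest reliability (ICC=0.98"). With r=0.98, T2 still needs 20 per group.
- The G*Power within-between interaction with two time points has f = d/4 and gives totals of 60, 30 and 42. With three time points and the full effect present at both follow-ups or at 12 weeks only, f = d/√18 and the totals are 54, 28 and 38.
- The three-time-point interaction run with f = d/2 returns total N of exactly 14, 8 and 10, the numbers printed as per-group n. That conversion is too large for a net difference in change.

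**Sensitivity of T2 to r** (values other than 0.97 and 0.98 are assumptions; the 12-week correlation may be lower than short-term reliability). On change scores, r = 0.98, 0.97, 0.95 and 0.90 need 20, 30, 48 and 95 per group. Power at 14 per group is 0.64, 0.48, 0.31 and 0.18.

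**Label of the T2 target.** With SD 27.9 and r=0.97, the standard error of measurement is 27.9×√0.03 = 4.83 ms. The usual individual-level 95% minimum detectable change is 1.96×√2×4.83 = 13.4 ms, not 5.1 ms. All three values carry the same citation.

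**The case against.** The strongest reply is that nobody plans trials of 16 or 20. The trial recruits 40 and allows for 28 completers, where pain has 0.78 to 0.87 power and is essentially adequate. Disability reaches 0.79 to 0.82 if everyone is retained. This stands: at the planned size only T2 is near one half, disability falls short once attrition is allowed for, and pain needs little or no qualification. It also stands that baseline-adjusted pain needs 24 in total against 16, so that shortfall is smaller than half.

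The origin of the stated numbers cannot be established from the document. The f = d/2 match is exact on all three outcomes but remains an inference. A dropped factor of 2 in the change variance comes close as well: 30, 14 and 20 by the normal formula, 32, 16 and 22 by the t.

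The minimum-detectable-change point depends on convention. T2 is measured per disc and per subregion, so 5.1 ms, 27.9 ms and 0.97 may not describe the same quantity. That is a request for clarification and does not affect the power figures, which use 5.1 ms whatever it is called.

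The β of 0.8 is a wording slip with no numerical effect. None of these replies makes 28, 16 and 20 follow from the inputs, or brings T2 to 80% power.

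**Conclusion.** The concern holds. The three stated requirements are wrong on the protocol's own figures. They are 47% to 53% of the need on change scores, and 48%, 67% and 50% (28/58, 16/24, 20/40) with baseline adjustment. Power at the stated sizes is 0.47 to 0.52 on change scores, rising only to 0.62 for pain if baseline-adjusted. At the planned 28 completers it is 0.48 for T2, 0.62 to 0.66 for disability and 0.78 to 0.87 for pain. T2 stays below 80% even with all 40 retained (0.63 to 0.64), so the statement that 40 recruits detect the target effect on every primary outcome is not supported.

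This rests on two-sided α of 0.05, equal groups, and the printed SDs and reliabilities taken as the between-person SD and the baseline-to-12-week correlation. One-sided testing and r=0.98, taken separately, leave the conclusion in place; a lower correlation makes T2 worse.

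**What to change.** Recruitment opened on 3 October 2022 with a target of 40, so keep that number and correct the justification in the Sample size section:

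1. Replace 28, 16 and 20 with the re-derived totals (60, 30 and 42 on change scores, or 58, 24 and 40 baseline-adjusted). State the formula, sidedness and G*Power test used.
2. For each primary outcome, report the power and the difference detectable with 80% power at 28 and at 40 completers, as tabulated above.
3. Remove the claim that 40 participants detect the smallest effect of interest on all three outcomes. Say plainly that T2 is underpowered for 5.1 ms.
4. Write power of 0.8 in place of β of 0.8.
5. Use one T2 reliability, or explain why 0.97 and 0.98 both appear. Reconcile 5.1 ms with SD 27.9 ms and r=0.97, or stop calling it the minimum detectable change.

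The cost is protocol and registry wording, through the route in the Protocol amendments section, and a less favourable power statement. No participants are added, and conduct and analysis do not change.

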### Recruitment

Potential participants will be initially contacted via web-based advertisements (eg, social media) and directed to a Deakin University website with a plain language statement and an option to express interest. Those who express interest will be screened via phone, and eligible participants will provide written informed consent before enrolment.

### Allocation

Participants will be randomly assigned (1:1) using block randomisation with random block lengths (between 2 and 6 per block) and stratification for sex to either intervention or waitlist control. A team member without contact with participants will obtain and employ the randomisation schedule (creating sequentially numbered, opaque, sealed envelopes). The randomisation schedule will be developed using the ‘blockrand’ package in R V.4.1.2 (https://www.r-project.org/).^75^

### Blinding

Given the nature of the intervention, neither participants nor team members administering the intervention will be blinded to treatment allocation. All objective outcomes of efficacy (eg, IVD health, pain-related inflammatory blood markers) will be collected by researchers blinded to treatment allocation. For subjective efficacy outcomes (eg, pain intensity, disability, kinesiophobia), the participant is considered the assessor and, therefore, not blinded to treatment allocation. Before data processing of objective measures of efficacy (eg, IVD T2), each participant will be allocated a random code to researchers who are blinded to treatment allocation. During data processing, researchers will also be blinded to the order of observations (baseline, 6 and 12 weeks post baseline). Following data processing, all biostatistical analyses will be blinded to treatment allocation and only revealed once all a priori analyses are completed.

### Data management

All data will be deidentified and stored on password protected servers at the institutions involved in the current study. All study-related electronic documents will be archived indefinitely at the institutions involved at the end of the study, which is in line with current ethical requirements. Only the researchers involved in this project will have access to the data collected.

Participation in the study is entirely voluntary, and withdrawal of consent will not jeopardise the relationship between the participant and any institution involved with the current project; thus, participant data are expected to be genuine. To minimise missing data, follow-up in-person testing will be booked at least 3 weeks in advance, and regular reminders will be provided to participants. Automatic electronic reminders will occur should the participant not complete follow-up questionnaires within 24 hours of receipt of the original notification. If questionnaires remain incomplete 48 hours after receipt, the participant will receive a phone call from a team member. Where data are deemed missing, linear mixed models can account for the absence of these data, and appropriate sensitivity analyses will be conducted to ensure all analyses meet these assumptions.

